### Outcome assessments

Participants will undergo reassessment at various intervals following enrolment, as outlined in
Table 3. Examinations will be conducted similarly to the baseline assessment. Adherence to treatment and symptoms, including side effects, will be queried and recorded at each follow-up. Trial medication adherence will be monitored by weighing eye drop bottles at specified follow-ups, with resupply provided as necessary. Visual acuity will be measured at each visit, with BSCVA assessed at the three-month follow-up (primary outcome measure). Quality of life questionnaires will be repeated at the final three-month follow-up. Slit-lamp examination and corneal photography will be performed at each visit. In vivo confocal microscopy will be repeated at specified intervals to assess fungal hyphae resolution. If the ulcer has not healed at the one-week follow-up, re-scraping for repeat culture will be conducted. Appointment cards will be provided for follow-ups, and transport costs will be covered for outpatient participants.

**Table 3. T3:** Baseline and follow-up assessment components.

Assessment Item	Baseline	Day 2	Day 7	Day 14	Day 21	Day 60	Day 90
History / Baseline questionnaire	X						
Check treatment adherence		X	X	X	X	X	X
Check for side effects		X	X	X	X	X	X
Visual Acuity – Presenting	X	X	X	X	X	X	X
Visual Acuity – BSCVA	X						X
Contrast Sensitivity	X						X
Slit-lamp Examination	X	X	X	X	X	X	X
Cornea Photography	X	X	X	X	X	X	X
*In vivo* confocal microscopy	X		X	X	X		
Cornea samples (Microbiology/PCR)	X		X				
Quality of Life Tools	X						X

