Secondary outcomes listed in
Table 4 will be analyzed using regression models appropriate for the data type, adjusting for any baseline imbalances. 

**Table 4. T4:** Secondary Outcome Measures that will be investigated as part of the trial, together with analysis details.

Secondary outcome measure	Details
Three-week BSCVA	We will analyze the secondary outcome of three-week Best Spectacle-Corrected Visual Acuity (BSCVA) in logMAR using the same methodology applied to the primary analysis of the primary outcome. The three-week BSCVA assessment will include values recorded between 18 days and 5 weeks, with the closest value to 3 weeks being selected.
Presenting VA by Peek	The presenting visual acuity (VA) assessed using Peek Acuity, with and without pinhole, will also be analyzed as a secondary outcome at three months. This measure will be particularly relevant if reliable BSCVA readings cannot be obtained at three months (e.g., if patients do not attend the clinic and at-home visual acuity testing is required). This analysis will follow the same approach as the primary analysis of the primary outcome. A sensitivity analysis, incorporating data from participants lost to follow-up, will use the most recent recorded observation of this variable.
Scar/infiltrate size at 1 week, 3 weeks and 3 months by slit lamp examination.	For scar or infiltrate dimensions, the geometric mean of the two principal axes (in mm) will serve as the outcome variable at one week, three weeks, and three months. The scar size, observed via slit lamp, will be compared between treatment groups at each time point using linear regression. This will include treatment arm and baseline infiltrate/scar size as predefined covariates, controlling for baseline differences.

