Key eligibility criteria	1. Acute MK characterised by: • Corneal epithelial ulceration >1mm diameter • Corneal stromal infiltrate • Acute inflammation: e.g. conjunctival injection, anterior chamber inflammatory cells, hypopyon. 2. Filamentous fungal hyphae visualised on smear microscopy and/or *in vivo* confocal microscopy. 3. Agree to be randomised to either treatment arm and able to give informed consent 4. Agree to be followed up at 2 days, 1 week, 2 weeks, 3 weeks, 2 months and 3 months 5. Adults (18 years and older)
Study type	Randomised controlled trial
Date of first enrolment	12 May 2021
Target sample size	358
Recruitment status	Recruiting
Primary outcome(s)	Best Spectacle Corrected Visual Acuity (BSCVA) at 3 months by a trial certified optometrist
Key secondary outcomes	1. Time to full epithelial healing (slit lamp examination by ophthalmic clinician). 2. Pin-hole visual acuity in logMAR at 3 months, trial-certified optometrist 3. Scar/infiltrate size at 1 week, 3 weeks and 3 months (slit lamp examination by ophthalmic clinician). 4. Ulcer depth at 1 week and 3 weeks (slit lamp examination by ophthalmic clinician). 5. Hypopyon height at 1 and 3 weeks, (slit lamp examination by ophthalmic clinician). 6. Perforation and/or TPK by three months (slit lamp examination by ophthalmic clinician). 7. Positive culture rate at 1 week 8. Ocular adverse effects at each follow up visit (Day 2, Day 7, Day 14, 3 weeks, 2 months, 3 months), slit lamp examination by ophthalmic clinician. 9. Quality of life (QoL) assessed using: EQ-5D, WHO/PBD-VF20, WHOQOL-BREF (comparison between baseline and QoL measures at 3 months) 10. Cost-effectiveness analysis, using EQ-5D data from 3 months and direct cost data. 11. Drug adherence at each follow up visit (Day 2, Day 7, Day 14, 3 weeks, 2 months, 3 months) whilst the patient is using study medications.

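### Table 4 analyses BSCVA at three weeks, but the visit schedule plans BSCVA only at baseline and Day 90, so this secondary outcome has no scheduled data

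*Protocol article*

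**What the plan says.** The first row of Table 4 (Analysis plan, secondary outcome analysis) reads: "We will analyze the secondary outcome of three-week Best Spectacle-Corrected Visual Acuity (BSCVA) in logMAR using the same methodology applied to the primary analysis". The window follows: "The three-week BSCVA assessment will include values recorded between 18 days and 5 weeks, with the closest value to 3 weeks being selected". The primary method, given earlier in the same section, is a linear regression with treatment arm and baseline BSCVA as covariates.

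The timing of acuity measurements is set under Outcome assessments. The text says: "Visual acuity will be measured at each visit, with BSCVA assessed at the three-month follow-up (primary outcome measure"). The columns of Table 3 are "Baseline Day 2 Day 7 Day 14 Day 21 Day 60 Day 90". The presenting acuity row, "Visual Acuity – Presenting X X X X X X X", has a mark in all seven columns. The BSCVA row, "Visual Acuity – BSCVA X X", has two marks, which stand under Baseline and Day 90; the five cells between them are empty. The same section also says, in general terms: "Examinations will be conducted similarly to the baseline assessment".

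Table 5 (under Ethics and consent) does not list three-week BSCVA. Its secondary acuity outcome is "Pin-hole visual acuity in logMAR at 3 months, trial-certified optometrist". The second row of Table 4 analyses presenting acuity by Peek Acuity at three months, with and without pinhole.

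**The concern.** An analysis plan cannot supply a measurement that the visit schedule leaves out. If sites follow Table 3, the three-week BSCVA analysis has nothing planned to work on. Any BSCVA taken outside the schedule in that window would come from a selected subset of participants, and the comparison would no longer be the randomised one that Table 4 describes.

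The timing matters too. Table 5 gives the recruitment status as recruiting, with first enrolment on 12 May 2021. A BSCVA not taken at Day 21 cannot be recovered later.

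The second, smaller issue is that Tables 4 and 5 describe three-month pin-hole acuity with different methods of measurement.

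**Working it through.** **Unaffected figures first.** The inputs from Sample size considerations are a difference of 0.2 logMAR, SD 0.62, two-sided alpha 0.0492, power 80%, and 1:1 allocation.

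- Per arm: n = 2 × (z for 1 − 0.0492/2 + z for 0.80)² × SD² / difference² = 2 × (1.967 + 0.842)² × 0.62² / 0.2² ≈ 151.6, rounded up to 152.
- Total: 2 × 152 = 304, with power 80.1%.
- With 15% dropout: 304 / 0.85 = 357.6, rounded up to 358.

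Both stated figures reproduce. They concern BSCVA at three months and do not depend on the three-week outcome.

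**Schedule against window.**

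1. Window in Table 4: day 18 to 5 weeks, that is day 18 to day 5 × 7 = 35.
2. Follow-up visits in Table 3: Days 2, 7, 14, 21, 60 and 90. Day 14 falls before the window and Day 60 after it. Only Day 21 lies inside.
3. Acuity measures by visit:

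| Measure (Table 3) | Baseline | Day 21 | Day 90 |
|---|---|---|---|
| Presenting acuity | marked | marked | marked |
| BSCVA | marked | not marked | marked |

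4. BSCVA measurements scheduled between day 18 and day 35: none. The nearest scheduled follow-up BSCVA, at Day 90, is 90 − 35 = 55 days after the window closes.
5. Participants with a scheduled BSCVA in the window: 0 of 358.

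**Could the table have been damaged in extraction?** This is unlikely. The sentence under Outcome assessments makes the same distinction as the table: acuity at every visit, BSCVA at three months. Table 5 also has no three-week BSCVA.

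**Pin-hole acuity.** Both tables place it at three months. Table 5 assigns it to a trial-certified optometrist. Table 4 has it only within the Peek Acuity row, and that row names no assessor. The time point agrees; the method does not.

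**The case against.** The strongest counter-argument is the general sentence that follow-up examinations resemble the baseline one. Baseline includes BSCVA (Table 2), so BSCVA at Day 21 could be implied, and the fault would then be an omitted mark in Table 3. That is possible, and the documents do not say which table is wrong. But the sentence describes how examinations are done, whereas the BSCVA row and the BSCVA sentence state when BSCVA is done, and the specific text governs. If the mark was simply omitted, Table 3 still needs correcting.

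Some stronger inferences are tempting, and the documents do not support them:

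- *No BSCVA will exist at three weeks.* The documents show only that none is scheduled. Sites may take it anyway, so the count of 0 of 358 describes the schedule and does not predict the data.
- *Presenting acuity would be labelled as BSCVA and adjusted for a refracted baseline.* Nothing in the article says so, and baseline presenting acuity is collected.
- *Pin-hole acuity would go unreported.* Table 4 covers it at three months through Peek Acuity. Only the method differs from Table 5.
- *The Peek outcome is unscheduled because Table 3 does not name it.* Table 3 lists measures, not instruments, and presenting acuity is marked at Day 90.

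On weight, it is fair to say that three-week BSCVA appears neither in the Objective section, nor among the abstract's secondary outcomes, nor in Table 5. That limits the consequence but does not remove the contradiction.

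**Conclusion.** The contradiction is confirmed. Table 4 defines a secondary outcome that needs a BSCVA between day 18 and day 35, and Table 3 and the accompanying text schedule none. As written, the outcome has no scheduled data for any of the 358 planned participants. This rests on reading the specific BSCVA row and sentence as governing over the general remark on follow-up examinations. It does not rest on any assumption about what sites actually do.

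The effect is confined to one secondary outcome. The primary outcome, its analysis and the sample size stand. The pin-hole discrepancy between Tables 4 and 5 is real but minor, and concerns only the method of measurement.

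**What to change.** First establish what sites do at Day 21, then make Tables 3 and 4 agree:

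- If BSCVA is measured at Day 21, mark it in Table 3. This is a wording correction and leaves the Table 4 outcome as it is.
- If it is not, redefine the Table 4 outcome as presenting visual acuity at Day 21, analysed by linear regression on treatment arm and baseline presenting acuity. Both measurements are already scheduled, so no new data collection is needed. The cost is a less refined measure than BSCVA. Because recruitment is under way, this should be dated and recorded as an outcome change.

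Starting BSCVA at Day 21 now would supply it only for participants who have not yet reached that visit.

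Separately, state one method for three-month pin-hole acuity and use it in both Table 4 and Table 5. This is a wording change if the chosen method is the one already in use.

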### Baseline assessment

The comprehensive baseline assessment is delineated in
Table 2. This encompasses clinical examination, corneal photography, in vivo confocal microscopy, and the procurement of microbiology samples. Additionally, participants will complete quality of life questionnaires, namely EQ-5D,24 WHO/PBD-VF20,25 and WHOQOL-BREF,26 with scoring details provided in
Table 2.

**Table 2. T2:** Baseline assessment. Assessment performed at baseline with details of how they are made.

Assessment	Details
Visual Acuity	Visual acuity, including Presenting, Pin-Hole, and Best Spectacle Corrected Visual Acuity (BSCVA), will be assessed using an ETDRS Tumbling-E logMAR 3m chart (Precision Vision, USA) mounted on an ESC 2000 ETDRS LED Cabinet (Precision Vision, USA). A trial-certified optometrist will perform these assessments separately for each eye.
Contrast Sensitivity	Contrast sensitivity will be evaluated using the Peek Contrast Sensitivity smartphone application, installed on an Android device (Sony Xperia Z3 Compact smartphone, Sony, Japan) ^ 24 ^.
Clinical Photographs	Photographs of both corneas will be taken using a Nikon D7500 camera equipped with an AF-S Micro Nikkor 105mm lens and SB-200 flash units (Nikon, Japan). A standardized protocol will be followed to ensure consistency in images across time points. Magnification will be standardized, enabling measurements of epithelial defects and stromal infiltrates.
Slit-lamp examination	A slit-lamp biomicroscope will be used to examine the anterior segment of both eyes, conducted by an ophthalmic clinician experienced in microbial keratitis management. Particular focus will be given to: 1. Eyelids: trichiasis, lagophthalmos, facial weakness, Bell’s reflex. 2. Suppuration. 3. Conjunctival inflammation. 4. Corneal sensation. 5. Corneal epithelial defects (including dimensions and ulcer depth). 6. Corneal inflammatory infiltrate characteristics: depth, size, profile, color, edge pattern, texture, satellites. 7. Anterior chamber inflammation: inflammatory cells, hypopyon, endothelial plaque. 8. Relative afferent pupillary defect.

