### Primary outcome measure

**
*Best Spectacle Corrected Visual Acuity (BSCVA) at Three Months:*
** Measured in logMAR units by a trial-certified optometrist, independent and masked to allocation. This outcome is selected for its functional significance and comparability with prior trials, including our recent Nepal trial
^
7,
16
^. Three months is chosen as it aligns with clinical experience indicating typical healing time for corneal ulcers. BSCVA will be assessed using an LED-backlit, Tumbling-E LogMAR chart under controlled conditions. Peek Acuity, a validated smartphone application, will be used if hospital visits are not feasible
^
32
^. LogMAR values for patients with CF vision or less will be applied, as previously described
^
33,
34
^.

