### Sample size considerations

The study is designed to test the hypothesis that natamycin combined with chlorhexidine is superior to natamycin alone in improving the primary outcome (BSCVA at 3 months). Assuming a BSCVA of 0.5 logMAR in the natamycin-only group, a standard deviation of 0.62 in both groups, and an adjusted alpha of 0.0492 (to accommodate interim analysis using the O’Brien-Fleming method), a sample size of 304 ensures 80% power to detect a 0.2 logMAR improvement. Allowing for a 15% dropout rate, the total target enrollment is 358 participants across both sites. 

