### Analysis plan

An intention-to-treat (ITT) approach will be used, analyzing all data based on the assigned randomisation group, regardless of adherence to the treatment protocol. Analyses will follow CONSORT guidelines for non-inferiority trials
^
35
^, and a flowchart will summarize recruitment, randomisation, and follow-up by treatment arm. Baseline characteristics will also be summarized. Details of the SPIRIT checklist are provided as Extended Data and available online (see Data Availability Statement). 

**
*Primary outcome analysis – unadjusted*
**

The primary outcome (BSCVA at 3 months) will be analyzed using linear regression, including baseline BSCVA and treatment arm as covariates. Mixed fungal and bacterial infections identified at baseline will be excluded from the primary analysis. We will use our alpha of 0.0492 to test the null hypotheses at 0.0492 significance. Significance will be assessed using a two-tailed test at 0.0492 level for assessing superiority.

**
*Primary outcome analysis – adjusted*
**

If baseline covariate imbalances occur between treatment arms, adjusted analyses will be conducted to ensure treatment effects are not confounded by these differences. This is particularly important if natamycin + chlorhexidine has a better outcome than natamycin, as the adjusted treatment effects may account for this observed imbalance whilst the unadjusted analyses may not. Sensitivity analyses will allow us to show that any observed positive treatment effect is not solely explained by imbalances at baseline in any of the covariates.

**
*Secondary analyses of the primary outcome*
**

- Per-Protocol Analysis: Re-analysis will be conducted excluding participants with significant deviations, poor adherence (<50%), or mixed/non-fungal infections. 

- Mixed Infections: Secondary analyses will include mixed infections using the same methodology as the primary analysis. 

- Sensitivity Analyses: Missing data will be addressed through multiple imputation or non-random missing data models if necessary. Additional sensitivity analyses will assess outcomes in subgroups such as those with severe vision loss, corneal perforation, or therapeutic keratoplasty. 

**
*Analysis of other determinants for success*
**

Logistic regression models will identify factors associated with poor outcomes (BSCVA >1.0 logMAR), adjusting for trial arm. Multivariate models will refine predictors based on likelihood ratio tests. 

**
*Secondary outcome analysis*
**

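### The sensitivity analysis of presenting acuity by Peek carries the last reading forward, although acuity can still change up to month 3 and no earlier Peek reading is scheduled

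*Protocol article*

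**What the plan says.** Table 4 (protocol article, Analysis plan) makes this a secondary outcome: "The presenting visual acuity (VA) assessed using Peek Acuity, with and without pinhole, will also be analyzed as a secondary outcome at three months". On the main analysis of that outcome it adds: "This analysis will follow the same approach as the primary analysis of the primary outcome". That means linear regression on treatment arm and the baseline value. For people lost to follow-up it then says: "A sensitivity analysis, incorporating data from participants lost to follow-up, will use the most recent recorded observation of this variable".

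For the primary outcome the same section takes a different route: "Missing data will be addressed through multiple imputation or non-random missing data models if necessary".

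On instruments, Table 2 (Baseline assessment) says: "Visual acuity, including Presenting, Pin-Hole, and Best Spectacle Corrected Visual Acuity (BSCVA), will be assessed using an ETDRS Tumbling-E logMAR 3m chart". The Outcome assessments section says of follow-up visits: "Examinations will be conducted similarly to the baseline assessment". Table 3 marks presenting acuity at baseline and on days 2, 7, 14, 21, 60 and 90. It names no instrument in that row and has no row for Peek. The Primary outcome measure section brings Peek in as a fallback: "Peek Acuity, a validated smartphone application, will be used if hospital visits are not feasible".

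**The concern.** There are two separate difficulties.

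The first is the method. The protocol chose three months because it matches the usual healing time of a corneal ulcer. The Treatment review section says topical therapy often lasts 4–6 weeks, and the Introduction says that about 25% of infections can go on to perforation and vision loss even on natamycin. A reading from the first days or weeks therefore describes an eye with an active ulcer, and the eye may later see better or worse. Entering that reading as the month-3 result treats a guess as an observation. A sensitivity analysis is meant to show whether losses matter, and one with an unknown bias of its own cannot show that well.

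The second is availability. The rule calls for an earlier value of the Peek variable, but the scheduled readings appear to be chart readings. An analyst would have to choose between leaving most lost participants out, which defeats the purpose, and carrying a chart value into a Peek outcome, which the plan does not mention.

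At stake is the usefulness of one supporting analysis, on the measure that Table 4 regards as most relevant when a clinic reading of corrected acuity cannot be had.

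**Working it through.** **Inputs from the protocol article.** Sample size considerations: target difference 0.2 logMAR, SD 0.62, alpha 0.0492, power 80%, 304 evaluable, 358 enrolled, and for losses "Allowing for a 15% dropout rate". Analysis plan: two-sided test. Randomisation and masking: 1:1 allocation.

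**The plan's own figure.** Per arm, n = 2 × (z for 0.0492 two-sided + z for 80% power)² × 0.62² / 0.2² = 2 × (1.967 + 0.842)² × 9.61 ≈ 151.6, so 152 per arm and 304 in total. Then 304 / 0.85 = 357.6, so 358. Both figures reproduce. They relate to the primary outcome; none is given for Peek acuity.

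**Illustration 1: equal loss in both arms.** Assume a true three-month difference on Peek of 0.2 logMAR. Let d be the proportion lost and f the share of that effect already present in the carried-forward values. The estimate becomes 0.2 × [(1 − d) + d × f].

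| d | f | Estimate (logMAR) |
|---|---|---|
| 5% | 0 | 0.190 |
| 10% | 0 | 0.180 |
| 15% | 0 | 0.170 |
| 15% | 0.25 | 0.178 |
| 15% | 0.50 | 0.185 |
| 15% | 1 | 0.200 |

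Under equal loss of 15% or less, with f between 0 and 1, the attenuation is at most 0.03 logMAR.

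**Illustration 2: unequal loss.** Let r be the carried value minus the value the same eye would have had at month 3, taken as common to both arms. The added shift in the arm difference is (d₁ − d₂) × r.
- 5-point difference, r = 0.3: 0.05 × 0.3 = 0.015 logMAR.
- 10-point difference, r = 0.5: 0.10 × 0.5 = 0.05 logMAR.
- 10% against 20%, r = 0.2 to 0.6: 0.02 to 0.06 logMAR in absolute size.

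The sign depends on which arm loses more. It reverses if the lost eyes would have worsened (r negative). The values of d by arm, f and r are all assumptions, as the article supplies none of them.

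**Is there a value to carry?** The statements fit together as follows.
- Table 2 assigns presenting and pinhole acuity to the ETDRS chart at baseline.
- Follow-up examinations are to resemble the baseline ones, which points to the chart again.
- Table 3 schedules presenting acuity at all seven time points but never mentions Peek.
- Peek is described as the substitute when a hospital visit cannot take place.

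Read literally, a lost participant has a Peek reading only if one happened to be taken outside hospital. If presenting acuity on any instrument is meant, a value exists for anyone measured at baseline, but it comes from a different instrument. The same gap touches the main Peek regression, which needs a baseline value of a variable with no scheduled baseline reading.

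**The case against.** The strongest reply is that little depends on this. The rule governs a sensitivity analysis of one secondary outcome. The main Peek analysis does not carry values forward, and Peek readings taken at home at month 3 are true three-month observations. Table 5 lists pinhole acuity by an optometrist among the key secondary outcomes and does not mention Peek. The Loss to follow-up section expects low losses and provides for phone contact and home visits. All of this stands, and it keeps the point minor.

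It can also be said that the two difficulties partly exclude each other: where no earlier value exists, nothing is carried and no bias arises. That is fair. They are alternative consequences of two readings of the rule and should not be added together. The illustrations above apply only where a value is carried.

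Further, Table 3 names no instrument, and use of the chart at follow-up is inferred from the statement that examinations resemble baseline. A fuller protocol may settle this. The inference is still the natural one from this text, and the carry-forward rule itself is stated outright.

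The article does not support four stronger readings that a reader might infer:
- That carrying forward is how the trial handles loss in general. The primary outcome has other methods.
- That the result is biased in a known direction. Some eyes recover and others deteriorate.
- That the standard error is bound to be too small. Counting 358 instead of 304 at an unchanged SD would shrink it by a factor of √(152/179) = 0.92, but carried early values may be more variable, so this is not established.
- That the main conclusion could be overturned. Nothing in the plan lets this check alter the primary test.

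**Conclusion.** The point holds as a minor one. The stated rule is last observation carried forward on an acuity that can still move either way up to month 3, so the check has a bias whose sign is unknown. Its size cannot be derived from the article. Under the assumed values it is at most 0.03 logMAR with equal loss up to 15%, and 0.015 to 0.06 logMAR with a 5- to 10-point difference in loss between arms. For scale, the standard error of the planned primary comparison is 0.62 × √(2/152) = 0.071 logMAR, so each of these shifts is below one standard error. The 0.2 logMAR benchmark belongs to best spectacle-corrected acuity and is only borrowed here.

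The instrument point also holds in limited form: Peek readings before month 3 are not scheduled, whereas presenting acuity is scheduled at every visit.

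**What to change.** In Table 4, replace the carry-forward sentence with multiple imputation by arm, or a repeated-measures mixed model, using the presenting acuities already scheduled at baseline and days 2, 7, 14, 21 and 60. This brings the outcome into line with the missing-data methods named for the primary outcome. State which instrument supplies presenting acuity at each visit, including the baseline covariate, and how chart and Peek readings are to be combined if both occur.

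The cost is a change of wording and a little more analysis work, with no new visits or measurements. Either method relies on data being missing at random given the earlier readings. The non-random missing-data models that the article already names can be used to probe that assumption.
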